# VITADIAL “Does correction of 25 OH-VITAmin D with cholecalciferol supplementation increase muscle strength in hemoDIALysis patients?”: study protocol for a randomized controlled trial

**DOI:** 10.1186/s13063-021-05302-9

**Published:** 2021-05-25

## Abstract

**Background:**

Muscle strength decreases as kidney failure progresses. Low muscle strength affects more than 50% of hemodialysis patients and leads to daily life activities impairment. In the general population, numerous studies have linked low 25OH-vitamin D (25OHD) concentrations to the loss of the muscle strength and low physical performances. Data on native vitamin D and muscle function are scarce in the chronic kidney disease (CKD) population, but low 25OHD levels have been associated with poor muscle strength. We present in this article the protocol of an ongoing study named VITADIAL testing if cholecalciferol supplementation in hemodialysis patients with low 25OHD improves their muscle strength.

**Methods/design:**

VITADIAL is a prospective open randomized French multicenter study. All patients will have 25OHD levels ≤50nmol/L at randomization. One group will receive 100,000 UI cholecalciferol once a month during 6 months; the other group will receive no treatment during 6 months.

In order to randomize patients with 25OHD ≤50nmol/L, supplemented patients will undergo a 3 months wash-out period renewable 3 times (maximum of 12 months wash-out) until 25OHD reaches a level ≤50nmol/L.

The main objective of this study is to analyze if a 6-month period of oral cholecalciferol (i.e., native vitamin D) supplementation improves muscle strength of hemodialysis patients with low 25OHD vitamin D levels. Muscle strength will be assessed at 0, 3, and 6 months, by handgrip strength measured with a quantitative dynamometer.

Secondary objectives are (1) to analyze 25OHD plasma levels after vitamin D wash-out and/or supplementation, as well as factors associated with 25OHD lowering speed during wash-out, and (2) to analyze if this supplementation improves patient’s autonomy, reduces frailty risk, and improves quality of life.

Fifty-four patients are needed in each group to meet our main objective.

**Discussion:**

In the general population, around 30 randomized studies analyzed the effects of vitamin D supplementation on muscle strength. These studies had very different designs, sizes, and studied population. Globally, these studies and the meta-analysis of studies favor a beneficial effect of vitamin D supplementation on muscle strength, but this effect is mainly found in the subgroup of aged patients and those with the lowest 25OHD concentrations at inclusion.

We reported a positive independent association between 25OHD and handgrip strength in a population of 130 hemodialysis patients in a dose-dependent manner. In our cohort, a plateau effect was observed above 75 nmol/L. Only two randomized studies analyzed the effect of native vitamin D supplementation on muscle strength in hemodialysis patients, but unfortunately, these two studies were underpowered. VITADIAL is a trial specifically designed to assess whether cholecalciferol might benefit to hemodialysis patient’s muscle strength.

**Trial registration:**

ClinicalTrials.govNCT04262934. Registered on 10 February 2020 - Retrospectively registered.

## Background

### Muscle strength in hemodialysis patients

It has been known for 50 years that chronic kidney disease (CKD) patients have low muscle strength and low physical exercise capacities [1, 2]. Muscle strength decreases as kidney failure progresses. Low muscle strength affects more than 50% of hemodialysis patients and leads to impairment on activities of daily living [3–5].

Body composition is also modified in hemodialysis patients: fat mass is increased and muscle mass is decreased [5, 6]. Our team has reported previously that 88% of patients in a hemodialysis center had low muscle strength but only 33% low muscle mass, suggesting that muscle strength might be due to low muscle fibers functioning more than muscle atrophy [5]. Striated muscle histological changes have been reported during kidney failure, with myofibrosis, fat inclusions within normal muscle fibers called myosteatosis, and type 2 fibers atrophy [7, 8]. Rapid contraction of striated muscle is mainly due to type 2 fibers, where type 1 fibers are essential for standing. Type 2 fibers are crucial to avoid falls. Other morphological anomalies have also been described in kidney failure: a reduced number of capillaries per number of fibers, a low number of mitochondria, mitochondrial dysfunction [8, 9]. Electrophysiological anomalies in peripheral motor nerves of hemodialysis patients are slight, with mainly a reduction in muscle relaxation following type 2 fibers atrophy [10]. These alterations lead to a reduced maximum oxygen consumption (VO2 max) with low muscle endurance as well as low muscle strength [11].

Numerous other factors have been proposed to explain the loss of muscle strength in CKD patients: protein energy wasting syndrome, lack of exercise, comorbidities, such as diabetes or heart failure, treatments, or uremic toxins [9, 12–14]. Within these factors, vitamin D deficiency has been proposed [15].

### Vitamin D and vitamin D insufficiency in hemodialysis patients

Native vitamin D deficiency (25OHD level <50 nmol/L) or insufficiency (level between 50 and 75 nmol/L) is very frequent in chronic kidney disease patients, with more than 80% having low serum 25OHD levels [16, 17]. Some observational data report an increasing rate of vitamin D deficiency with worsening of kidney function where other studies report serum vitamin D levels comparable in patients with CKD and patients with normal kidney function [18, 19].

Many causes and risk factors have been associated with low 25OHD levels in hemodialysis patients: age, female gender, high adiposity, low physical activity, and diabetes mellitus [16]. Interestingly, metabolism of vitamin D is also modified in uremic patients in some specific ways: reduced vitamin D receptor (VDR) and increased CYP24A1 levels, impaired 25OHD tubular resorption, reduced skin synthesis of vitamin D [20, 21].

In CKD patients, native vitamin D is less transformed into active 1–25 vitamin D—namely calcitriol—because 1α-hydroxylation is mainly performed by the kidney, but almost every cell type is able to produce 1α-hydroxylase and to act in an autocrine or paracrine manner. Native vitamin D supplementation increases 25OHD levels, but also calcitriol levels in the CKD population [22, 23]. Moreover, although 25OHD has a low affinity for the vitamin D receptor (VDR), in the plasma, its concentration is at least 100 times higher than the calcitriol concentration. Therefore, native vitamin D is important as it might have different metabolic effects than calcitriol, including in skeletal muscle cells [22, 24].

### Effects of vitamin D on muscle strength in the general population

Vitamin D deficiency is common in the general western population, with at least 50% of the population affected according to the Workshop Consensus for Vitamin D Nutritional Guidelines [25]. This proportion reaches 80% of the French adult population according to the recent epidemiological French studies [26]. Beyond the classical effects on bone metabolism, vitamin D regulates numerous physiological effects. Vitamin D receptor is expressed among almost all cellular types including muscle cells [27]. In vitro, 25OHD is implicated in myoblast cell proliferation in culture. In rats, vitamin D injection is implicated in the recruitment, proliferation, and differentiation of satellite cells into mature muscle fibers and is essential for wounding repair [28]. Vitamin D is not only necessary for muscle repair, but is also required for mature muscle fiber contraction and mitochondrial metabolism [29].

In the general population, numerous observational studies have linked low 25OHD concentrations to the loss of the muscle strength and low physical performances, to a higher incidence of falls, to muscle pain, and to myosteatosis [30–37]. These observational studies led to the realization of around 30 randomized studies analyzing the effects of vitamin D supplementation on muscle strength. These studies had different designs, sizes and non-homogenous studied populations [38]. Moreover, their results regarding vitamin D are sometimes inconclusive because of the different type**s** of vitamin D supplementation or the association with calcium supplements [39]. Globally, these studies and the meta-analysis of studies favor a beneficial effect of vitamin D supplementation on muscle strength, but this effect is mainly found in the subgroup of the most aged patients and those with the lowest 25OHD concentrations at inclusion [38, 39]. To note, if vitamin D supplementation has any effect, it could be mainly observed in the population with vitamin D deficiency, i.e., with the lowest 25OHD [40]. This is an important clue since many studies regarding vitamin D supplementation have been performed in patients with normal or non-measured 25OHD concentrations, and fail to show any improvement of muscle strength [41, 42]. These latter results must not be extrapolated to the population with low 25OHD [39].

Regarding the risk of falls, a first meta-analysis published in 2004 including 1237 participants concluded that vitamin D supplementation reduced risk of falling by 22% (corrected OR, 0.78; 95% confidence interval [CI], 0.64–0.92) compared to calcium or placebo [43]. This study included only 5 studies. Since then, a larger meta-analysis which included 37 randomized trials (*n*=34144) did not find any effect analysis of supplementation on falls, but this meta-analysis included heterogeneous studies, many of them did not report baseline 25OHD concentrations or had normal baseline 25OHD [44].

Could vitamin D supplementation be deleterious for muscle function? This question has been raised by an Australian study in 2256 women aged over 70 years old who received 500,000 UI cholecalciferol supplementation yearly and in which the incidence of falls was higher in the group of patients with supplementation [45]. The design of this study was criticized because it led to high 25OHD concentrations. Nevertheless, two other studies have raised concerns on high doses and the risk of femoral neck fractures or falls [46, 47].

### Effects of vitamin D on muscle strength in the hemodialysis population

Data on native vitamin D and muscle function are scarce in the CKD population, and most interventional studies have been performed with calcitriol or vitamin D analogs such as paricalcitol [48–55].

Few studies reported an association between low 25OHD and low muscle strength in hemodialysis patients [56]. In 25 hemodialysis patients, Boudville et al. reported a positive correlation between 25OHD levels and quadriceps strength, even if most patients were taking calcitriol therapy [24]. We reported a positive independent association between 25OHD and handgrip strength in a population of 130 hemodialysis patients in a dose-dependent manner [15]. Interestingly, in our cohort, a plateau effect was observed above 75 nmol/L.

Only two randomized studies analyzed the effect of native vitamin D supplementation on muscle strength, but unfortunately, these two studies are underpowered. Marckman et al. randomized 52 CKD patients of which 27 hemodialysis patients with 25OHD < 50nmol/L to an 8-week long treatment of 40,000 UI cholecalciferol per week or placebo. Cholecalciferol had no effect on muscle function (secondary objective) in this small study [57]. In the second study, Hewitt et al. included 60 hemodialysis patients with 25OHD < 60nmol/L to 50,000 UI cholecalciferol or placebo, once per week during 8 weeks and then once per month during 4 months. This study failed to show any difference in muscle strength of upper and lower limb or functional performances between supplemented and not supplemented patients [58].

So far, no study has been published that had calculated the number of patients to include in order to show an effect of native vitamin D on muscle strength in hemodialysis patients. For this reason, we set up the VITADIAL study. VITADIAL is a prospective randomized trial designed to assess whether cholecalciferol supplementation improves hemodialysis patient’s muscle strength.

## Methods

### Study design and setting

VITADIAL is a prospective open randomized French multicenter study. Serum 25OHD levels will be ≤ 50 nmol/L at randomization. Vitamin D group will receive 100,000 UI cholecalciferol once a month during 6 months; control group will receive no treatment during 6 months (Fig. 1).

**Fig. 1 Fig1:**
[figure not shown]
Study design. 25OHD: 25-hydoxyvitamin D; VitD: Vitamin D

In France, hemodialysis patients with low 25OHD are often supplemented with cholecalciferol. Thus, to randomize patients with 25OHD ≤ 50nmol/L, supplemented patients will undergo a 3 months wash-out period renewable 3 times (maximum of 12 months wash-out) until serum 25OHD reaches a level ≤ 50nmol/L.

Patients with 25OHD ≤ 50nmol/L at inclusion will directly be randomized. Patients with 25OHD > 50nmol/L at inclusion will undergo wash-out and be randomized as soon as 25OHD is ≤ 50nmol/L. Patients with 25OHD still > 50nmol/L after 12 months of wash-out will be excluded of the study (Fig. 1).

### Objectives and judgment criteria

The main objective of this study is to analyze if a 6-month period of oral cholecalciferol (i.e., native vitamin D) supplementation improves muscle strength of hemodialysis patients with low 25OHD vitamin D levels. Muscle strength will be assessed by handgrip strength measured with a quantitative dynamometer (Kern, Germany). Measures will be performed on both arms before the hemodialysis session in a standardized procedure. Handgrip strength measurement is a well validated evaluation of muscle strength in the hemodialysis population [15, 59, 60].

Secondary objectives are (1) to analyze 25OHD plasma levels after vitamin D wash-out and/or supplementation, as well as factors associated with 25OHD lowering speed during wash-out, and (2) to analyze if this supplementation improves patient’s autonomy, reduces frailty risk, and improves quality of life. Patient autonomy will be measured by the Activities of Daily Living-Katz index which is a standardized measure of biological and psychosocial function [61]. Frailty risk will be measured by the auto questionnaire Frail-Non-Disabled FIND which is validated scoring method of frailty risk [62]. Quality of life will be measured by the Kidney Disease Quality Of Life scoring method (KDQoL-SF™) [63].

### Study intervention

Study protocol is described in Table 1. All patients of participating dialysis centers will be screened for inclusion and non-inclusion criteria. If every inclusion criterion is met, but no non-inclusion criterion, investigators will inform patients and collect their written informed consent.

**Table 1 Tab1:** Study procedures

	Screening	Inclusion	Wash-out phase	Treatment/no treatment (random phase)		
	V1	V2	V3 and/or V3bis and/or V3ter and/or V3quater	V4/M0	V5/M3	V6/M6
Check of selection criteria	✓					
Patient information	✓	✓				
Check of inclusion criteria		✓				
Consent Form Signature		✓				
Socio-demographic data		✓				
Clinical data		✓	✓	✓	✓	✓
Biological data		✓	✓	✓	✓	✓
Including 25OHD, iPTH, calcemia, phosphor		✓	✓	✓	✓	✓
Randomization				✓		
Dispensation treatment/no treatment				✓	✓	✓
Main criterion: handgrip		✓	✓	✓	✓	✓
Secondary criteria: ADL, FIND, KDQOL scores				✓	✓	✓
Compliance			✓	✓	✓	✓

During the wash-out period, all vitamin D supplementation (native or active) will be suspended. All other medical treatments and dialysis prescriptions will be maintained as usual care. 25OHD will be measured every 3 months as well as handgrip strength. If 25OHD lowers or equals to 50 nmol/L, the patient will be randomized. If not, the patient will continue wash-out for 3 additional months. After 12 months of washout, if 25OHD remains > 50 nmol/L, the patient will be excluded.

After randomization, muscle strength will be measured at baseline (at randomization) and 3 and 6 months. Variation of muscle strength at randomization and at the end of the study will be compared in the two groups.

During the treatment period, patients randomized in the cholecalciferol group will receive 100,000 UI oral cholecalciferol every month during 6 months, but no other vitamin D supplementation; patients randomized in the control group will receive no vitamin D at all. Medication will be provided to dialysis facilities; it will be given by the investigator at the end of dialysis session in the dialysis facility and the medication will be traced by the investigator. All other medical treatments and dialysis prescriptions will be maintained as usual care. Muscle strength will be measured at randomization, 3 and 6 months. Secondary judgment criteria will be measured at randomization and the end of the study. After 6 months with or without cholecalciferol supplementation, the study will end.

During the whole study, intact parathyroid hormone (iPTH), calcium and phosphate will also be measured every 3 months to screen for adverse events.

### Study population and sample size

CKD Patients on hemodialysis for more than 3 months, aged over 18 years old, who gave their consent will be included (Table 2).

**Table 2 Tab2:** Inclusion, non-inclusion, and drop-out criteria

Inclusion criteria: - Under hemodialysis for more than 3 months - Aged over 18 years old - Gave their consent	
Non-inclusion criteria: - Non-fluent French speaker - Incapacity to provide consent or to answer questionnaires - Pregnancy or breast feeding - Cognitive impairment - Bedridden or life expectancy <1 year - Active cancer - Uncontrolled hyperparathyroidism as defined by the K-DIGO (iPTH >9x normal laboratory maximal value), cinacalcet treatment or hypocalcemia <2.0 mmol/L or hypercalcemia >2.7mmol/L - Past osteoporosis fracture - Treatment with active vitamin D - Unable to perform handgrip measurement - 25OHD >50nmol/L without vitamin D treatment - Cholecalciferol intolerance or allergy	
Drop out criteria: - 25OHD >50nmol/L after 12 months wash-out - Hypercalcemia >2.7mmol/L - Hyperparathyroidism (iPTH >9x normal laboratory maximal value) during wash-out or after randomization if patient is in the no treatment group - Hypoparathyroidism (iPTH <3x normal laboratory lower value) in a patient receiving cholecalciferol - Cholecalciferol intolerance or allergy - Death, renal transplantation - Pregnancy - Consent withdrawal - Renal recuperation allowing hemodialysis to stop - Unability to perform handgrip	

Inclusion, non-inclusion and drop-out criteria are described in Table 2. Hyperparathyroidism was defined as the Kidney Disease Improving Global Outcome (KDIGO) by an iPTH level >9 times the upper normal limit of the assay [64].

Sample size was calculated in order to meet our main objective and based on an observational study showing a dose-dependent correlation between 25OHD and muscle strength measured by handgrip [15]. In this study, mean muscle strength was 13 ± 8 kg in patients with 25OHD < 50 nmol/L and 18 ± 8 kg in patients with 25OHD > 75 nmol/L. To show a 5-kg difference between the two groups, considering a standard deviation of 8 kg, an α-risk of 0.05, and a power of 0.9, the number of patients required is 54 patients in each group (*t* test comparison of 2 independent means, https://marne.u707.jussieu.fr/biostatgv/). The study will continue until 110 patients will reach the end of the study according to the protocol.

In order to achieve recruitment, all hemodialysis patients from participating centers will be screened for eligibility every three months (concomitant to PTH and vitamin D dosages). The study will be proposed to all patients with inclusion criteria and no non-inclusion criteria. If recruitment in participating centers is not sufficient, more centers should be included in the study.

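### Calcium below 2.0 mmol/L bars entry but neither stops wash-out nor bars randomisation, although wash-out withholds all vitamin D

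*Protocol article*

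**What the plan says.** All references are to the protocol article.

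- **Entry (Study population and sample size, Table 2).** The non-inclusion list names both calcium limits, alongside uncontrolled hyperparathyroidism: "cinacalcet treatment or hypocalcemia <2.0 mmol/L or hypercalcemia >2.7mmol/L".
- **Drop-out (same table).** The calcium and high-iPTH items read "Hypercalcemia >2.7mmol/L - Hyperparathyroidism (iPTH >9x normal laboratory maximal value) during wash-out or after randomization if patient is in the no treatment group". The other items are 25OHD still too high after 12 months, low iPTH under cholecalciferol, intolerance or allergy, death or transplantation, pregnancy, withdrawn consent, renal recovery and inability to do the handgrip test. Low calcium is not among them. The text presents the table as the rule set: "Inclusion, non-inclusion and drop-out criteria are described in Table 2".
- **Leaving wash-out (Study intervention).** "If 25OHD lowers or equals to 50 nmol/L, the patient will be randomized". "If not, the patient will continue wash-out for 3 additional months". Study design and setting agrees: patients above the threshold "will undergo wash-out and be randomized as soon as 25OHD is" at or below 50 nmol/L.
- **Vitamin D withheld (Study intervention).** Native and active forms are both suspended in wash-out, and "patients randomized in the control group will receive no vitamin D at all".
- **Monitoring.** Under Study intervention, iPTH, "calcium and phosphate will also be measured every 3 months to screen for adverse events". Biological dosing says that the 3-monthly values serve to find drop-out criteria or to see whether a patient can be randomised. The Discussion relies on calcium, phosphate and iPTH for safety in wash-out and in the untreated arm.

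**The concern.** The trial treats calcium below 2.0 mmol/L as a reason not to start. For supplemented patients with 25OHD above 50 nmol/L, starting means months of wash-out before the randomisation decision, so calcium may have changed by then. The article itself names calcium as a safety marker for the phases without vitamin D, yet only a high value has a stated consequence.

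What is at stake is patient safety and consistent eligibility. A patient at a calcium level that the trial refuses at entry could be kept in wash-out, or be randomised with the possibility of a further 6 months without vitamin D.

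**Working it through.** The plan gives no figure on this point, and its sample size (54 per group) does not depend on it. The check is a comparison of the rules, followed by simple addition of durations.

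**Step 1. Set the Table 2 limits side by side.**

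| Condition | Bars entry | Stops wash-out | Stops a control patient |
|---|---|---|---|
| Calcium >2.7 mmol/L | yes | yes | yes |
| iPTH >9x upper limit | yes | yes | yes |
| Calcium <2.0 mmol/L | yes | no | no |

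Of these three laboratory conditions, low calcium is the only one not carried forward. The iPTH rule does not cover it. The entry list joins iPTH and calcium with 'or', so each excludes on its own, and a patient with calcium below 2.0 mmol/L and iPTH at or under 9 times the limit meets no drop-out criterion.

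**Step 2. Look for a rule elsewhere that would catch the patient.**

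- Table 1 ticks selection criteria at V1 and inclusion criteria at V2 only. No eligibility re-check is ticked at the V3 visits or at V4/M0.
- The randomisation rule in Study intervention and in Study design and setting depends on 25OHD alone.
- Biological dosing sends the 3-monthly values to two uses, drop-out criteria and the possibility of randomising. Low calcium is not among the first and not a stated bar to the second.
- Adverse-event screening means that a low value would be seen. The article attaches no stop to it.

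**Step 3. Follow a wash-out patient who enters within the calcium limits and falls below 2.0 mmol/L at a V3 visit.**

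- 25OHD >50 nmol/L: wash-out continues for 3 more months, unless the 12-month limit has been reached.
- 25OHD ≤50 nmol/L: the patient is randomised 1:1. Allocation to control means 6 further months without vitamin D.

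**Step 4. Add the durations.**

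- Wash-out: 3 months at least; 3 + 3 × 3 = 12 months at most.
- Wash-out followed by control: 3 + 6 = 9 to 12 + 6 = 18 months without vitamin D.

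These are times without vitamin D under the design. They are not times with low calcium.

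**Step 5. Check that the fix needs no new data.** Table 1 ticks calcium at V2, at each wash-out visit, and at V4/M0, V5/M3 and V6/M6. The value is available at every decision point.

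**The case against.** Entry and withdrawal criteria serve different purposes and need not mirror each other. Other treatments continue as usual care, so low calcium can be treated without vitamin D. The risk is also partly covered: patients on active vitamin D are not included, and high iPTH stops wash-out and control patients. The Discussion considers these phases to be of low clinical risk and says that supplementation is not standard in all countries. Finally, this is a condensed article, and the full protocol (V5.0) may say how abnormal safety results are handled.

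Much of this stands. Asymmetry alone would not be a finding. It becomes one here because the missing limit concerns a marker on which the article relies for the safety of these phases, and because the list does contain an iPTH stop written for them. Condensation does not explain the gap in wash-out and at randomisation, since Table 2 is offered as the list of criteria and runs to details such as renal recovery. For handling low calcium in a control patient after randomisation, the objection is stronger: that may well be settled in the full protocol.

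Three stronger readings are tempting and are not supported.

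- A reader might infer that low calcium would go untreated. The text withholds vitamin D only.
- A reader might combine the earliest low result, the slowest fall in 25OHD and allocation to control into one long exposure. That stacks worst cases and says nothing about how long calcium would stay low under usual care.
- A reader might extend the point to every entry criterion missing from the drop-out list. The article relies on none of those for safety in the phases without vitamin D, and no consequence can be shown for them.

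**Conclusion.** The point holds for wash-out and for the decision to randomise. As printed, calcium below 2.0 mmol/L does not stop wash-out or prevent randomisation, although it would have prevented entry. Patients randomised directly go through the entry check without a wash-out in between, so the gap mainly concerns supplemented patients with 25OHD above 50 nmol/L at inclusion.

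The size is limited. The article gives no frequency of calcium below 2.0 mmol/L in wash-out, so the number affected is unknown. A reader might infer bias between the arms or lost power; nothing in the document supports either, and neither is claimed. The conclusion assumes that Table 2 reproduces the drop-out criteria of the full protocol, as the article presents it. On that basis this is an inexpensive safety improvement worth making. It does not challenge the trial's validity.

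**What to change.** 1. Add to the drop-out criteria in Table 2: *Hypocalcemia <2.0 mmol/L during wash-out*.
2. In Study intervention, make randomisation conditional on calcium of 2.0–2.7 mmol/L at V4/M0 as well as on 25OHD ≤50 nmol/L.
3. Unless the full protocol already settles it, state that a control patient whose calcium falls below 2.0 mmol/L after randomisation may receive rescue vitamin D, which is recorded. The patient stays in follow-up, has handgrip measured at M6 and is analysed in the allocated arm, in line with the intention-to-treat principle under Statistical analysis. This should not be a drop-out criterion. Say also whether such patients count toward the 110 who are to complete the study according to the protocol.

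No new measurement is needed. A few patients would be lost before randomisation and have to be replaced, and rescue in a few controls would slightly reduce the contrast between arms. Under Protection of human subjects, an amendment needs the agreement of the ethics committee and the authorities, and new written consent from participants already included. With recruitment due to finish by 01/01/2022 (Trial status), the change helps only patients not yet past these decision points or still in follow-up.

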### Statistical analysis

A flow-chart diagram will describe the number of patients by status (inclusion, drop-out, randomization, follow-up). Patient characteristics will be described by treatment groups: qualitative data will be expressed as number and percentages, and quantitative data as mean and 95% confidence interval. Comparison between the two groups will be performed using the Chi-2 test for qualitative variables and the Student test for quantitative variables. If conditions to use these tests are not met, comparisons will be performed using appropriate non-parametric tests (Fischer’s exact test, Mann-Whitney test). Analyses will be considered as significant if *p* value is ≤ 0.05, in a bilateral situation.

The main objective will be analyzed by comparing muscle strength variation during the treatment period (M0–M6) between treated (receiving cholecalciferol) and non-treated group using a covariance analysis in which principal analyzed effect will be the treatment group and will be included as covariables the initial muscle strength, the study center, age stratification (< or ≥ 70 years old), and gender. Principal analysis will be based on intention to treat principle.

Secondary analyses will compare the ADL, FIND, and KDQOL scores between the two treatment groups using the same statistical method (analysis of covariance). The decreased of 25OHD plasma level will be described at the end of the wash-out period (mean change from inclusion and number of patients with 25OHD ≤ 50 nmol/l). To analyze factors associated with 25OHD lowering speed, a linear (or the most appropriate function) mixed model (random intercept and/or slope) will be performed including variables potentially related to 25OHD changes, such as but not limited to age, gender, BMI, diabetes, and duration of previous 25OHD treatment.

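### Inability to do the handgrip test is a drop-out criterion with no limit to the pre-randomisation period, so it can withdraw randomised patients on the primary endpoint itself and sits badly with intention to treat

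*Protocol article*

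**What the plan says.** All references are to the protocol article.

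- **Study population and sample size, Table 2.** The non-inclusion list contains "Unable to perform handgrip measurement". The drop-out list contains, as a separate entry, "Unability to perform handgrip", with no study phase and no cause attached. Another entry in the drop-out list, hyperparathyroidism, does name its phases: "during wash-out or after randomization if patient is in the no treatment group".
- **Study intervention, Table 1.** Handgrip is tested at inclusion, during wash-out, and at M0, M3 and M6.
- **Objectives and judgment criteria.** "Measures will be performed on both arms before the hemodialysis session in a standardized procedure".
- **Statistical analysis.** The main objective is analysed by covariance analysis, "comparing muscle strength variation during the treatment period (M0–M6) between treated (receiving cholecalciferol) and non-treated group". The same section adds: "Principal analysis will be based on intention to treat principle".
- **Study population and sample size, text.** "The study will continue until 110 patients will reach the end of the study according to the protocol".

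**The concern.** Before randomisation the criterion is sensible, since a patient who cannot do the test cannot supply the endpoint. After randomisation it makes withdrawal depend on the endpoint. If a patient becomes unable to squeeze because strength has declined, the rule ends participation at just the point where the outcome is informative. It also merges that patient with one who has an injured or recently operated limb, although the two call for different handling and the second may still be testable on the other side.

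The effect on the data is outcome-dependent missingness. If cholecalciferol preserves strength, more controls than treated patients would reach inability, and the remaining controls would look stronger than the group really is. If it harms strength, the same mechanism would understate the harm. An analysis plan can choose how to impute a missing M6 value, but it cannot recover M6 tests or reasons that were never collected because participation had ended.

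**Working it through.** **1. Does the criterion reach randomised patients?** It names no phase. Other entries in the list do, and at least one applies explicitly after randomisation. The Biological dosing section describes checks for drop-out criteria in both the wash-out and the treatment phase. Handgrip is tested at M3, after randomisation. So the criterion can be met at M3. On the ordinary meaning of drop-out, the patient then has no M6 value.

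**2. Does it conflict with the analysis?** The analysis variable is the change from M0 to M6 and the principle is intention to treat. Recruitment, however, is counted in patients who finish according to the protocol, so drop-outs are in effect replaced. Every drop-out criterion shares this tension. This one is special because its trigger is the primary test.

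**3. The plan's own figure.** Inputs are a difference of 5 kg, SD 8 kg, two-sided α 0.05 and power 0.90.

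n per group = 2 × (1.960 + 1.282)² × 8² / 5² = 2 × 10.51 × 2.56 = 53.8, rounded up to 54.

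This matches the stated 54. An exact t test gives 54.8, so 55. The point here does not change that figure.

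**4. Size if inability follows strength and the unable are excluded.** The article gives no inability rate, test threshold, SD of change or drift, so all four are assumed. Baseline is normal with mean 13 and SD 8 kg (the planning values for 25OHD below 50 nmol/L), truncated at the threshold. M6 = M0 + drift + effect + random change, and a patient is unable when M6 falls below the threshold. With a 3 kg threshold, covariance analysis without the unable compares as follows with scoring them 0 kg:

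| Change SD, drift (kg) | True 5: excluded / scored 0 | Loss | True 2: excluded / scored 0 | Loss |
|---|---|---|---|---|
| 4, 0 | 4.73 / 5.03 | 6% | 1.85 / 2.01 | 8% |
| 4, −2 | 4.59 / 5.00 | 8% | 1.78 / 1.98 | 10% |
| 6, 0 | 4.40 / 4.94 | 11% | 1.70 / 1.95 | 13% |
| 6, −2 | 4.22 / 4.87 | 13% | 1.62 / 1.91 | 15% |

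Loss = 1 − excluded / scored 0; for example 1 − 1.62/1.91 = 15%. Inability is 6–14% in controls and 1–9% in treated patients.

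Other assumptions give less:
- Threshold 0 kg, other inputs unchanged: about 2–6%.
- Threshold 1–2 kg with change SD 2–4 kg: about 1–7%.
- No true effect: no bias.
- True effect of −2 kg with the 3 kg threshold: exclusion gives about −1.5 to −1.8 kg.

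**5. Size if inability rates are set freely by group.** Take 18 and 13 kg among testable patients and score the unable 0 kg. The difference is (1 − pT) × 18 − (1 − pC) × 13, against 5.00 kg when they are omitted.

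- pC 10%, pT 2%: 17.64 − 11.70 = 5.94 kg.
- pC 2%, pT 2%: 17.64 − 12.74 = 4.90 kg.
- pC 2%, pT 10%: 16.20 − 12.74 = 3.46 kg.

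So the direction is towards no effect when inability arises from strength itself. It can go either way when inability differs between groups for other reasons.

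**The case against.** A reader might infer that these patients leave the comparison and that intention to treat therefore cannot hold. The documents do not say so. Table 2 also lists death, transplantation and consent withdrawal, so it catalogues why participation ends and does not define the analysis population. The stated population is intention to treat, which can accommodate imputation, a worst score or ranks. The rule for a missing M6 value may stand in an analysis plan that is not shown, and its absence from an article is no fault.

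A reader might also equate inability with extreme weakness. Table 2 gives no cause, and a very weak patient who attempts the test can register a low value. Bedridden patients and those with life expectancy under one year are not included, which makes true inability within six months less likely. Nothing says that inability on one side alone triggers drop-out.

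The upper part of the range is fragile. The normal curve puts Φ((3 − 13)/8) = 11% of patients below 3 kg, but it also puts Φ(−13/8) = 5% below 0 kg, which is impossible. A lognormal with the same mean and SD puts about 1% below 3 kg.

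Finally, a 0 kg score given only for weakness would rest on a cause judged by unblinded staff, in a trial whose open design is defended on the ground that the endpoint needs no interpretation.

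All of this stands. It rules out any claim of a known bias and argues against a cause-based 0 kg score as the primary rule. It does not remove the printed rule, which can end follow-up of a randomised patient on the primary test.

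**Conclusion.** The point holds as a stated rule that works against the stated analysis, and it should be changed. The drop-out criterion is not limited to the wash-out, it can withdraw randomised patients for a reason tied to the primary endpoint, and a patient unable at M3 would have no M6 value. The per-protocol completion target makes the fit with intention to treat worse.

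The size cannot be fixed from the documents. If such patients were excluded and inability followed strength, the effect would shrink by roughly 1–15%, towards no effect. That range rests on assumed thresholds of 0–3 kg, change SDs of 2–6 kg, drift of 0 to −2 kg and a normal baseline. It is an illustration and not a bound, since another baseline shape would move it. The documents do not support saying that drop-outs are deleted or that inability means weakness.

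**What to change.** 1. In Table 2, limit the handgrip drop-out criterion to the period before randomisation.
2. After randomisation, keep the patient in follow-up and attempt handgrip at M6, even if the M3 test could not be done. This concerns follow-up and measurement only; whether study treatment continues is a separate clinical matter.
3. If only one side cannot be tested, use the testable side and compare it with the same side at M0. Both sides are measured already.
4. Record the reason for any inability.
5. Keep these patients in the intention-to-treat analysis. Add a sensitivity analysis that gives inability the worst rank (or 0 kg), once for all inability and once for inability attributed to weakness, because cause is judged by unblinded staff.

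The cost is one changed line in Table 2, one more case report form field and one more sensitivity analysis. The section Protection of human subjects also commits the sponsor to ethics committee and health authority agreement, and to renewed consent, for any protocol amendment. Recruitment began in 2018, so M6 values already lost under the present rule may not be recoverable. Those patients should be reported by group with the reason.
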